## Abstract

**Background:**

Many shift workers suffer from sleep issues, which negatively affect quality of life and performance. Scientifically evaluated, structured programs for prevention and treatment are scarce. We developed an anonymous online cognitive behavioral therapy for insomnia (CBT-I) program. After successful completion of a feasibility study, we now start this prospective, randomized, controlled superiority trial to compare outcomes of two parallel groups, namely an intervention group and a waiting-list control-group. Additionally, we will compare these outcomes to those of a face-to-face CBT-I outpatient sample.

**Methods:**

Collaborating companies will offer our anonymous online intervention to their shift-working employees. Company physicians and counseling services will screen those interested for inclusion and exclusion criteria. Participants will receive access to our online service, where they will complete psychometric assessment and receive random assignment to either the intervention group or the waiting-list control group. Participants and providers will be aware of the group assignment. We aim to allocate at least *N* = 60 participants to the trial. The intervention consists of psychoeducation, sleep restriction, stimulus control, relaxation techniques, and individual feedback delivered via four e-mail contacts. During the intervention, as well as during the waiting period, participants will fill out weekly sleep diaries. Immediately after completion of the program, the post-intervention assessment takes place. Participants in the control group will be able to participate in the program after all study assessments. To recruit an additional sample, collaborating outpatient sleep clinics will provide six sessions of standard face-to-face CBT-I to an ad hoc sample of shift working patients. We expect both the online and the face-to-face CBT-I interventions to have beneficial effects compared to the control group on the following primary outcomes: self-reported symptoms of depression and insomnia, sleep quality, and daytime sleepiness.

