The purpose of this study is to evaluate the effects of online CBT-I in shift workers, compared to a waiting-list control group and face-to-face CBT-I. Specifically, we hypothesize both CBT-I interventions to be associated with greater improvements than the control condition regarding the following outcomes: sleep efficiency as reported by the participants in sleep diaries [34]; symptoms of depression as measured by the Beck Depression Inventory (BDI-II) [35]; symptoms of insomnia as measured by the Regensburg Insomnia Scale (RIS) [36]; and daytime sleepiness as measured by the Epworth Sleepiness Scale (ESS) [37].

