After registration, T0 measurements and randomized allocation, participants in both of the online groups will receive access to the first weekly sleep diary along with instructions on how to proceed. Every time participants in the online intervention group complete a week of diary entries, they will receive the next e-mail with individual feedback and further CBT-I contents. In the face-to-face intervention, participants will fill out sleep diaries between sessions. We will encourage participants to leave as few nights undocumented as possible; however, breaks in the sleep protocols will be permitted. Following our experience from the feasibility study, we expect that participants complete the program within 6 to 12 weeks. We will consider an intervention complete after a participant has received all CBT-I contents and filled out at least 4 weeks of sleep diaries.

T0 will include screening questions for sleep issues such as periodic limb movement disorder, sleep apnea, and sleepwalking, as well as questions regarding concurrent and previous treatments. Changes in medication will be reported in the sleep diaries. We will not exclude participants from the trial based on these questions; however, we might recommend alternative courses of treatment and we will control for relevant changes in treatment or medication during the trial when analyzing the data.

Outcome measures of the study will include data from at least four sleep diaries (total sleep time and time in bed for each night, average sleep efficiency across seven consecutive nights) as well as psychometric self-report scales at T0 and T1. The BDI-II is a 21-item self-report measure for depressive symptoms [35]. The RIS is a 10-item self-report questionnaire for cognitive, emotional, and behavioral aspects of psychophysiological insomnia [36]. The ESS is an 8-item self-report scale for daytime sleepiness [37]. In addition, T0 will include the 15-item self-report Morningness-Eveningness-Stability-Scale improved (MESSi) [39], from which the individual chronotype will be calculated, as well as three screening questions for sleep apnea, snoring, and periodic limb movement disorder. This will be used to guide the CBT-I treatment and explore potential differences in treatment response [40].

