**Table 2 Tab2:**
[figure not shown]
Schedule of enrolment, interventions, and assessments as recommended by the Standard Protocol Items: Recommendations for Interventional Trials (SPIRIT) statement [41]

*Optional CBT-I and T2 after waiting list not shown here in the interest of readability

The effect size for the CBT-I treatment in our feasibility study [29] (*n* = 22) was *d* = 0.76, corresponding to *f* = 0.38. The correlation among the repeated measures reached a value of *r* = .67. Setting the *α*-error probability at .05, *β*-error probability at .20, the number of groups at 3, and the number of measurements at 2, we calculated a required sample size of *N* = 15 using the ANOVA repeated measures, within-between interaction setting of the G*Power software [42]. If we adjust the effect size to a more conservative *f* = 0.25, the required sample size is *N* = 30. Consistent with this magnitude, Bortz and Schuster [43] recommend a sample size of at least *N* = 19 for large effect sizes, high power values, and low α-error probabilities. Expecting a maximum dropout rate of 50%, as observed in the feasibility study, we aim to allocate 60 participants and evaluate at least 30 participants (10 per group). We will make an effort to obtain assessments for participants who drop out of the study to facilitate carrying out intention-to-treat analyses.

Company physicians and social counseling services at collaborating companies will inform their workforce about the trial and screen those interested for eligibility. They will use flyers and posters to reach as many potential participants as possible, for example on company health days. They will also be the ones to obtain informed consent before granting access to our anonymous online platform. No personal information about potential or enrolled trial participants will be shared with the investigators. Vice versa, investigators will not share personal information with the company physicians and social counseling services. Exceptions to this rule are groups of at least ten participants, where sample characteristics, such as the average rate of improvement, may be communicated to the enrolling services in collaborating companies. No such data will be shared if inferences to individual cases are possible at any level or if any subsample of interest is smaller than ten.

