## Discussion

The prevalence of sleep disorders among shift workers is high, yet evidence-based programs for prevention and treatment of these problems in this target population are scarce. Providing a low threshold to treatment by transferring CBT-I contents to an online platform and testing the efficacy with a randomized design seems profitable for potential participants as well as our field of study.

One of the limitations of this design is the lack of a scheduled follow-up measurement 6 to 12 months after T1. If we find positive results for our treatment, we will not be able to attest to the sustainability of these results. However, in order to contact former participants after the trial, we would have to collect personal information such as phone numbers or email addresses, which would be in direct conflict with our promise of an explicitly anonymous platform. Future studies could address the long-term effects of online CBT-I. Another limitation concerns the non-randomized allocation between the face-to-face and the online settings. We will thus have to remain mindful of potential confounding factors and remain very cautious in comparing online and face-to-face group outcomes. There are multiple reasons as to why we chose to allocate participants in this manner. Firstly, collaborating companies are distributed across all of Germany, making it impossible for some of the potential participants to realistically reach one of the outpatient clinics for regularly scheduled appointments. Secondly, we promise anonymous treatment on our online platform, which we could not offer in a face-to-face setting.

We hope that the results of this study contribute to the growing evidence on the efficacy of online CBT in general and online CBT-I in shift workers in particular. If effective, our intervention offers a low-threshold, cost-effective, and readily transferrable approach to treatment and prevention of sleep disorders in the shift working population that decreases symptoms of depression and insomnia and improves daytime sleepiness.

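### Four unranked primary outcomes, one without an instrument, no success rule, and a sample size tied to no named outcome leave the primary claim open to selection

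*Protocol article*

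**What the plan says.** The Methods paragraph of the abstract lists "primary outcomes: self-reported symptoms of depression and insomnia, sleep quality, and daytime sleepiness". It expects benefit on these for two comparisons: "We expect both the online and the face-to-face CBT-I interventions to have beneficial effects compared to the control group".

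The last paragraph of the Introduction also lists four outcomes, but does not call them primary. Three match the abstract and are given instruments (BDI-II, RIS, ESS). The fourth is "sleep efficiency as reported by the participants in sleep diaries", where the abstract has sleep quality.

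The outcomes paragraph of the Methods describes the diary data as "total sleep time and time in bed for each night, average sleep efficiency across seven consecutive nights", next to the three questionnaires. It ranks nothing and names no measure of sleep quality.

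The sample size paragraph (after Table 2) uses one effect size, d = 0.76, equated with f = 0.38. The feasibility study supplied it for the CBT-I treatment, and no outcome is attached. The paragraph continues "Setting the *α*-error probability at .05", with beta "error probability at .20" and "the number of groups at 3, and the number of measurements at 2". This is the only place where an alpha appears.

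The analysis text specifies repeated measures ANOVA. The Discussion says that the intervention, if effective, "decreases symptoms of depression and insomnia and improves daytime sleepiness". It does not define effective, and the fourth outcome is absent from that sentence.

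**The concern.** A primary outcome fixes in advance which result decides the trial. Here four results have that status, one of them cannot be identified with certainty, and no rule links them to a conclusion. An author who found a difference on one outcome only could report the trial as positive without departing from the text. So could an author who chose either reading of sleep quality.

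The setting makes this matter more. Participants and providers know the allocation, every outcome is self-reported, and only 10 participants per group need be evaluated.

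The sample size has a related weakness. It is a calculation for one test of one outcome, but the reader cannot tell which. The Introduction reports that the feasibility study improved both insomnia and depression, so d = 0.76 could describe either.

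**Working it through.** **1. The outcome lists side by side**

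| Concept | Abstract (called primary) | Introduction (not ranked) | Instrument in Methods |
|---|---|---|---|
| Depression | yes | yes | BDI-II |
| Insomnia | yes | yes | RIS |
| Daytime sleepiness | yes | yes | ESS |
| Sleep quality | yes | no | none named |
| Sleep efficiency | no | yes | sleep diary |

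**2. The plan's own sample size**

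Inputs from the sample size paragraph: k = 3 groups, m = 2 measurements, r = .67, alpha .05, power 80%. For the within-between interaction, λ = f²·N·m/(1 − r), with df1 = (k − 1)(m − 1) and df2 = (N − k)(m − 1).

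- f = 0.38, N = 15: λ = 0.1444 × 15 × 2/0.33 = 13.1; power 82.0%.
- f = 0.25, N = 30: λ = 0.0625 × 30 × 2/0.33 = 11.4; power 82.1%. (N = 29 is the minimum; 30 gives equal groups.)
- Dropout of 50%: 30/(1 − 0.5) = 60 allocated.

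The stated figures reproduce. They hold for one outcome tested at .05.

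**3. False positives over four outcomes, online versus waiting list**

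Assumptions that are not in the protocol: each outcome is tested at two-sided .05, one success suffices, and the four test statistics share a common correlation. The protocol gives no between-outcome correlation, so a range is shown.

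Independent tests: any difference, 1 − .95⁴ = .185; in favour of CBT-I, 1 − .975⁴ = .096. Correlated normal test statistics were simulated with 2,000,000 draws:

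| Correlation | Any false positive | In favour of CBT-I |
|---|---|---|
| 0 | 18.5% | 9.6% |
| .3 | 17.4% | 8.7% |
| .5 | 15.5% | 7.8% |
| .7 | 13.1% | 6.5% |

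With t tests at 10 per group (18 df), any false positive runs from 18.5% to 13.4%. A single test has 5% in either direction and 2.5% in favour of CBT-I. The directional rate is therefore 6.5/2.5 = 2.6 to 9.6/2.5 = 3.8 times that of a single test.

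**4. The opposite rule: all four must succeed**

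The chance of a false claim is then at most 5%, because every outcome, including any without a true effect, must pass its own test. Power pays instead. For the randomized pair with 20 evaluated and f = 0.25, λ = 0.0625 × 20 × 2/0.33 = 7.6, and power is 74% for one outcome. For four independent outcomes it would be .74⁴ = 30%; positive correlation would raise this, up to 74% at most.

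**5. Cost of adjusting across four outcomes**

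The strictest Holm step is .05/4 = .0125. At f = 0.25:

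- Randomized pair, 20 evaluated: power falls from 74% to 51%.
- Three-group calculation: N = 40, or 42 with equal groups, in place of 30. At 50% dropout that is 80 to 84 allocated in place of 60.

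**The case against.** The protocol never says that each outcome is tested at .05 or that any one success is enough. Its wording leans towards joint success: the Introduction hypothesizes improvement on the whole list, and the Discussion joins its outcomes with an "and". A multiplicity procedure is also commonly left to a statistical analysis plan, which is not shown here. All of this stands. It makes the error rates conditional, and the absence of an adjustment procedure is not the point. What remains is fixed in this document: four co-equal primaries, one named differently in two places, and a sample size for an unnamed outcome.

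Three stronger readings are tempting and not supported:

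- *That the chance of a false claim of efficacy is 13–19%.* That figure counts differences in either direction, and the planned ANOVA is non-directional. In favour of CBT-I it is about 7–10%.
- *That counting both contrasts gives eight tests and a 34% error rate* (1 − .95⁸). The contrasts share the waiting-list control, so independence is impossible. With the shared control the rate is about 32% at zero correlation between outcomes and 23% at .7. The face-to-face group is also a non-randomized ad hoc sample, where confounding matters more than alpha.
- *That splitting alpha cuts power from 51% to 28%.* This takes 0.76 as the standardized between-group difference at one time point, with r = .67, which departs from the protocol's own f. At f = 0.25 the fall is from 74% to 51%, and at f = 0.38 from 98% to 91%.

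**Conclusion.** The point holds in conditional form. The protocol leaves its primary claim open to selection among four outcomes, one of which it does not identify consistently, and its sample size belongs to no stated outcome. If each outcome is tested at two-sided .05 and one success suffices, the chance of at least one false-positive primary outcome for the randomized contrast is about 13–19%, of which about 7–10% favours CBT-I. Both ranges rest on assumed correlations of .7 to 0. If all four must succeed, there is no inflation and the cost falls on power. The protocol does not say which rule applies.

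Confidence is high on the inconsistency and the missing ranking, which can be read directly. It is lower on the size, which depends on rules and correlations that the document does not give.

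**What to change.** By a dated amendment, made before outcome data are examined by arm:

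1. Name one primary outcome for online versus waiting list at two-sided .05. The RIS at T1 is a reasonable choice: it measures insomnia and has a baseline taken before allocation. The BDI-II and ESS share that baseline, so it separates the RIS only from the diary.
2. Make the other outcomes secondary, tested in a fixed order or with Holm. If all four stay primary, apply Holm across them.
3. Treat the non-randomized face-to-face contrast as secondary.
4. Use sleep efficiency consistently in place of sleep quality.
5. State which outcome d = 0.76 describes.

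Cost: three outcomes become secondary, and the amendment must be communicated to the registry, ethics committee and sponsors. Recruitment began in November 2019 and providers are unblinded, so the amendment should record its date and that no outcome data had been examined by arm. With one primary outcome, the multiplicity fix itself needs no extra participants. Keeping four with Holm costs power at the strictest step: 74% to 51% for the randomized pair at f = 0.25 with 20 evaluated.

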**Conclusions:**

The online intervention allows shift workers to follow a CBT-I program independently of their working schedule and location. Forthcoming results might contribute to further improvement of prevention and therapy of sleep issues in shift workers.

**Trial registration:**

German Clinical Trials Register DRKS DRKS00017777. Registered on 14 January 2020—retrospectively registered.

## Trial status

Protocol version: v1.1, 01/12/2021

The study began recruitment on 11/01/2019. We plan to complete recruitment by 05/31/2022.

## Introduction

While working during the day is still the standard in western society, about one in six workers is on a shift schedule [1, 2], a proportion that has remained largely constant since 1985 [3]. Shift work is associated with various health complaints, including cardiovascular, gastroenterological, and oncological diseases, as well as sleep disorders like insomnia and circadian rhythm sleep disorder [4–7]. Factors that cause sleep issues in shift workers include psychosocial stress [7, 8], negative health behaviors [9], and circadian misalignment [10, 11]. Approximately one in three shift workers suffers from at least one clinically relevant sleep disorder, most often closely related to the individual shift schedule [10, 12–14]. If such a disorder persists for more than 3 months, the International Classification of Sleep Disorders [15] refers to it as “shift work sleep disorder” (SWSD). There exists some evidence on how to prevent SWSD by ergonomic redesign of work environments, mostly focused on the topics of bright artificial light during night shifts, nap breaks, and changes in shift rotation [16]. However, formulating clear guidelines presents a challenge to researchers because of conflicting evidence on most of these topics. For manifest SWSD, treatment options described in the literature are almost always limited to pharmacological approaches, most prominently including the use of melatonin [17–19].

The standard treatment of sleep disorders not related to shift work is cognitive behavioral therapy for insomnia (CBT-I) [20, 21], which has consistently shown sustained moderate to large positive effects [22]. CBT-I has also been successfully applied in shift workers in two published studies [23, 24], where Järnefelt and colleagues have shown the potential for group delivered CBT-I interventions in participants who worked irregular hours and suffered from insomnia or SWSD. However, we argue that many shift workers might not be able to participate in regularly scheduled group or even one-on-one meetings due to their working hours. For the treatment of shift workers, we thus argue for a transfer of CBT-I contents from synchronous face-to-face to asynchronous online modes of communication, which do not rely on simultaneous presence of provider and recipient [25]. Multiple studies have shown the transfer of CBT-I contents to online settings to be feasible and effective in reducing insomnia symptoms, both in non-shift workers [26–28] and shift workers [29]. Improvements in sleep tracking and dropout rate management, as well as more validation studies and expanded public access, are needed [30, 31].

Our group conducted a non-randomized feasibility and non-inferiority trial on the effects of an online CBT-I intervention (*n* = 22) compared to a face-to-face setting (*n* = 20) [29]. We were able to show significant improvements regarding symptoms of insomnia and depression in both settings. Contents of the program are rooted in the CBT-I literature [32, 33] and have largely remained the same for this study. Based on the findings in the feasibility study, we adjusted the online platform and the study design in order to reduce the dropout rate and to increase the validity and transferability of the results. We will now begin to evaluate the efficacy of the online CBT-I intervention in a randomized controlled trial. In this manuscript, we present a description of the updated study protocol.

The purpose of this study is to evaluate the effects of online CBT-I in shift workers, compared to a waiting-list control group and face-to-face CBT-I. Specifically, we hypothesize both CBT-I interventions to be associated with greater improvements than the control condition regarding the following outcomes: sleep efficiency as reported by the participants in sleep diaries [34]; symptoms of depression as measured by the Beck Depression Inventory (BDI-II) [35]; symptoms of insomnia as measured by the Regensburg Insomnia Scale (RIS) [36]; and daytime sleepiness as measured by the Epworth Sleepiness Scale (ESS) [37].

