## Methods

This prospective, controlled, superiority trial compares outcomes of two parallel groups, namely an online intervention group and a waiting-list control group, randomly assigned in a 1:1 ratio, and a third, non-randomized ad hoc sample, namely a face-to-face intervention group.

Data for the online intervention group and the control group will be collected at the Institute for E-Counselling, University of Applied Sciences Nuremberg Georg-Simon-Ohm, Germany. The Institute is a department of the Faculty for Social Sciences. It is specialized in developing, implementing, and evaluating online counseling solutions. The partnering companies that will offer the online intervention to their employees include multiple plants of a large German engineering and technology company and two German municipal hospitals. Data for the face-to-face intervention group will be collected at the outpatient clinic for sleep medicine at the University Clinic for Psychiatry and Psychotherapy, Paracelsus Medical University Nuremberg, Germany, as well as partnering outpatient sleep clinics across Germany.

For the online conditions, participants are included starting in November 2019 and ending in May 2022, according to the eligibility criteria listed in Table 1. Prior to granting access to the online platform, company physicians or social counseling services will obtain informed consent. Participants will be anonymous to the CBT-I professional.

**Table 1 Tab1:** Eligibility criteria for participants

Inclusion criteria	
Age ≥ 18	
Regularly (> 6 times per month) working outside the hours of 6 a.m. to 10 p.m.	
Subjective sleep issues diagnosed in the screening process	
Exclusion criteria	
Acute suicidality as measured by the respective item in the BDI-II at T0	
Ongoing alcohol or drug abuse	
No access to required technology (PC, smartphone, tablet)^a^	

^a^Only applies to online conditions

For the face-to-face condition, collaborating clinics will include participants from August 2020 to May 2022. Most of the same eligibility criteria apply (see Table 1).

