Figure 1 and Table 2 illustrate the design of the study. For the online arms of the trial, company physicians and social counseling services in collaborating companies will screen those interested for eligibility. We describe inclusion and exclusion criteria in Table 1. Psychometric assessments are carried out on the online platform after logging on for the first time (T0) and after filling out the last of four weekly sleep diaries (T1). Immediately after T0, participants are allocated randomly in a 1:1 ratio to the intervention or the control group. The intervention group will receive the CBT-I contents via e-mail between their weekly sleep diaries (W1 through W4). After completing T1, participants in the waiting group will be able to follow the CBT-I program. If they choose to do so, they will complete at least four more sleep diaries during the CBT-I period and we will contact them for a follow-up (T2) after completion. For the face-to-face arm, psychologists and CBT-I professionals in collaborating outpatient sleep clinics will screen their patients for eligibility according to the criteria in Table 1. Psychometric assessments are carried out right before the first (T0) and right after the last session (T1) (see Table 2).

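### The superiority hypothesis and the only powered test include the non-randomised face-to-face sample, so a significant 3-group interaction would not show that online CBT-I works

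*Protocol article*

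**What the plan says.** The protocol article describes the confirmatory comparison in several places.

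- **Introduction, hypotheses:** "we hypothesize both CBT-I interventions to be associated with greater improvements than the control condition". Online and face-to-face CBT-I appear side by side, each against the waiting list.
- **Abstract, Methods:** the same pairing is attached to the primary outcomes: "We expect both the online and the face-to-face CBT-I interventions to have beneficial effects compared to the control group on the following primary outcomes".
- **Abstract, Background:** the trial is a randomised comparison of two parallel groups, with the face-to-face comparison added to it.
- **Methods, design:** besides the two randomised groups there is "a third, non-randomized ad hoc sample, namely a face-to-face intervention group". It comes from outpatient sleep clinics and is recruited from August 2020; the online groups come from companies and are recruited from November 2019. Both streams close in May 2022.
- **Methods, allocation:** randomisation covers only the other two groups: "participants are allocated randomly in a 1:1 ratio to the intervention or the control group".
- **Methods, sample size (after Table 2):** "Setting the *α*-error probability at .05, *β*-error probability at .20", with "the number of groups at 3, and the number of measurements at 2", "using the ANOVA repeated measures, within-between interaction setting of the G*Power software". The result is at least 30 evaluable participants, 10 in each of three groups.
- **Methods, data handling and analysis:** group comparisons and superiority tests are to use repeated measures ANOVA. No contrast is singled out.
- **Discussion, limitations:** because allocation between the settings is not random, the authors will "remain very cautious in comparing online and face-to-face group outcomes".

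**The concern.** Two comparisons of different evidential standing are put under one superiority hypothesis. Online versus waiting list is protected by randomisation. Face-to-face versus waiting list is not: the groups differ by design in setting, recruitment route and part of the calendar period, so a difference between them cannot be attributed to treatment.

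The sized test makes this worse. A 3-group interaction asks whether mean change differs anywhere among the three groups. It can be significant solely because the clinic sample changed differently, for whatever reason. If that result were read as the trial's superiority result, online CBT-I could be credited with an effect that the randomised data do not show.

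**Working it through.** **1. Reproduce the plan's sample size.**
Inputs from the sample size paragraph: α = .05, power 80%, k = 3 groups, m = 2 measurements, r = .67, f = 0.38 or 0.25.
Formula (within-between interaction): λ = f²·N·m/(1 − r), with df = (k − 1)(m − 1) and (N − k)(m − 1).
- f = 0.38, N = 15: λ = 0.1444 × 15 × 2 / 0.33 = 13.13, df 2 and 12, power 82.0%.
- f = 0.25, N = 30: λ = 0.0625 × 30 × 2 / 0.33 = 11.36, df 2 and 27, power 82.1%.
- Dropout: 30 / (1 − 0.5) = 60.

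All the stated figures reproduce. The arithmetic is sound; the question is what the sized test tests.

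**2. The 3-group test when online CBT-I does nothing.**
With two time points, the group-by-time F test equals a one-way F test on change scores. In baseline SD units the variance of change is 2(1 − .67) = 0.66 (SD 0.812). Let mean change be 0 for waiting list, 0 for online and d for face-to-face, with n per group. Then λ = n × (2/3) × d² / 0.66, df 2 and 27 for n = 10. The values of d are assumptions, because the article gives no face-to-face effect. The 0.76 is borrowed from the feasibility study's effect size.

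| d (assumed) | λ at n = 10 | P(significant) |
|---|---|---|
| 0.25 | 0.63 | 9.5% |
| 0.5 | 2.53 | 25% |
| 0.76 | 5.83 | 52% |
| 1.0 | 10.10 | 77% |

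A simulation of 100,000 trials gives 25% at d = 0.5 and 52% at d = 0.76.

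The power at the design value depends only on f, not on which group produces it. Setting λ = 11.36 gives d² = 11.36 × 0.66 × 3/20 = 1.125, so d ≈ 1.06. The planned 82% is reached in full even if the clinic sample alone supplies the effect.

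**3. The direct randomised contrast in the same scenario.**
In the same simulation, the online versus waiting-list contrast rejects in about 5% of trials at d = 0.5 and at d = 0.76. A significant omnibus followed by a significant online versus waiting-list contrast occurs in 3.8% (d = 0.5) and 4.5% (d = 0.76).

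**4. Power when only the randomised groups are tested.**
Same formula with k = 2:
- N = 20 (10 + 10): λ = 0.0625 × 20 × 2 / 0.33 = 7.58, df 1 and 18, power 74.0%.
- N = 24 (12 + 12): λ = 9.09, df 1 and 22, power 82.2%. At 50% dropout this is 24 / 0.5 = 48 randomised.

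**5. T0 as covariate.**
Relative to change scores, ANCOVA multiplies the variance of the randomised contrast by (1 − r²)/(2(1 − r)) = (1 + r)/2 = 0.835. With an assumed between-arm difference in change of 0.76 SD, simulation (allowing for chance baseline imbalance) gives power of about 51% for change scores and 55 to 56% for ANCOVA at 10 per arm; at 15 per arm, about 70% and 75 to 76%. These are lower than the 74% in step 4 because f = 0.25 with two groups corresponds to a difference of 1.0 SD: λ = (10/2) × 1.0² / 0.66 = 7.58.

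**The case against.** The strongest reply is that the article never declares the 3-group omnibus to be the decisive test. It speaks of comparisons and superiority tests in the plural, its hypothesis consists of two directional predictions that an omnibus F cannot answer, and the Abstract's Background defines a two-group randomised trial. The contrasts may be set out in an analysis plan that is not shown. This stands in part: the omnibus reading is inferred from the sample size paragraph and the joint hypothesis. But the omnibus is the only test sized, and the face-to-face superiority claim is explicit and stays confounded however the contrasts are computed.

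A reader might infer that online CBT-I faces a 52% false-positive rate. The documents do not support that. If the clinic sample truly changes differently, the omnibus null is false and 52% is power against it; the direct randomised contrast stays at 5%.

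A reader might also infer that clinic patients enter more severely affected and regress further toward the mean. No baseline data by setting are given, and most of the same eligibility criteria apply. Setting, recruitment route and start date are the documented differences.

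The Discussion's caution can be read generously. The article uses the word online for both randomised arms, so a caveat about the online setting may be meant to include the waiting list. It does not say so, and face-to-face versus waiting list is the comparison that is hypothesised.

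Finally, with two randomised groups a group-by-time ANOVA is valid. ANCOVA is a gain in precision, not a correction.

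**Conclusion.** The concern holds in this form: the article states a confounded comparison as a superiority hypothesis next to the randomised one, and sizes the trial on a test that mixes them. A significant 3-group interaction would not establish that online CBT-I works. With no online effect, it would appear in about 25% or 52% of trials at 10 per group if the clinic sample's change differed by 0.5 or 0.76 SD. Those figures rest on assumed clinic differences, r = .67, equal variances and the documented minimum of 10 evaluable per group. Any non-zero clinic difference acts in the same direction.

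The randomised comparison itself is intact and can be tested with the stated method. What needs repair is which test is confirmatory and what is claimed for the face-to-face sample.

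**What to change.** - In the Abstract, the Introduction's hypotheses, the sample size paragraph and the analysis paragraph, name online versus waiting list in randomised participants as the confirmatory test. Analyse T1 by ANCOVA with T0 as covariate and report the difference with its 95% CI. The group-by-time ANOVA limited to the two randomised groups is an acceptable alternative, at a loss of roughly 5 to 6 points of power.
- Take face-to-face out of the superiority hypothesis. Report it as within-group change with CI and, at most, an exploratory baseline-adjusted comparison.
- Extend the Discussion's caution explicitly to face-to-face versus waiting list.
- Restate power for two groups. On the plan's own f = 0.25 and r = .67, 10 + 10 evaluable gives about 74%; 80% needs 12 per arm, or 48 randomised at 50% dropout.

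The cost is that no confirmatory claim is made for face-to-face, which the design could not support, and that the power statement must be rewritten, with at least 12 evaluable per randomised arm if the 80% target is kept.
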